# Levosimendan in Cardiac Arrest (LeiCA): Protocol for a Randomized, Double‐Blind, Phase II Clinical Trial

**DOI:** 10.1111/aas.70159

**Published:** 2025-11-24

## Abstract

**Background:**

Despite developments in advanced life support, outcomes after out‐of‐hospital cardiac arrest (OHCA) remain poor. Levosimendan, a calcium‐sensitizing inodilator commonly used in heart failure, has shown beneficial effects in several experimental models and anecdotal clinical cases of cardiac arrest. The Levosimendan in Cardiac Arrest (LeiCA) pilot trial will evaluate levosimendan as an adjunct to advanced life support in refractory OHCA.

**Methods:**

This will be an investigator‐initiated, randomized, double‐blind, placebo‐controlled, single‐center pilot trial. Patients aged 18–75 years with witnessed, nontraumatic, refractory OHCA in Stockholm County, Sweden, will be eligible for enrollment by a physician‐staffed emergency medical service unit. Forty patients will be randomized in a 3:1 ratio to receive a single intravenous bolus of either levosimendan 2.5 mg (*n* = 30) or placebo (*n* = 10), administered during cardiopulmonary resuscitation via prefilled, masked syringes. Both groups will receive routine advanced life support and postresuscitation care as applicable. Included patients eligible for hospital transfer will be admitted to Karolinska University Hospital in Solna, Stockholm, Sweden. The primary endpoint is 30‐day survival. Secondary endpoints include additional clinical outcome measures.

**Conclusion:**

The LeiCA pilot trial will investigate the effects of levosimendan as an adjunct to advanced life support for refractory OHCA. The results will inform the design of a definitive multicenter trial.

**Trial Registration:**

ISRCTN15862521; October 22, 2025

## Introduction

1

Out‐of‐hospital cardiac arrest (OHCA) affects approximately 6000 individuals annually in Sweden, yet overall 30‐day survival remains below 14% [1]. Beyond early cardiopulmonary resuscitation (CPR) with chest compressions and defibrillation, few pharmacological interventions have demonstrated improved long‐term outcomes [2]. Epinephrine, and amiodarone for shockable rhythms, remain standard components of advanced life support [3], despite no clear evidence of improved neurological outcomes [4, 5]. Moreover, epinephrine's effect size on survival appears modest [6], and may be even smaller in patients with initial shockable compared to nonshockable rhythms [7]. Amiodarone may increase survival to hospital admission relative to placebo [8], although this finding has been challenged [5].

The pathophysiology of cardiac arrest is complex, involving global ischemia and subsequent reperfusion injury. Postcardiac arrest syndrome, characterized by myocardial dysfunction, brain injury, and systemic inflammation, is another major contributor to poor outcomes [9]. Contemporary evidence suggests that current pharmacotherapy using epinephrine may exacerbate these processes by impairing cerebral microcirculation and thus worsening outcome [10, 11].

Levosimendan is a calcium sensitizer and inodilator [12], with documented efficacy and safety in acute decompensation of chronic heart failure [13, 14]. Its applications have expanded to various other clinical conditions and settings [15, 16]. With regard to cardiac arrest, experimental data suggest that levosimendan may facilitate ROSC [17, 18, 19], improve postresuscitation cardiac function [20, 21, 22, 23, 24, 25, 26], and enhance survival [20, 25, 27, 28] and neurologic recovery [24, 29]. Clinical reports recount successful application in refractory cases [30, 31, 32], and for postresuscitation myocardial dysfunction [33, 34, 35]. Its favorable safety profile and potential to mitigate the postcardiac arrest syndrome make it a promising candidate for further investigation in OHCA.

Given the lack of recent advances in resuscitation pharmacology, and the promising preclinical data on levosimendan, we propose a pilot trial to explore the 30‐day survival after intra‐arrest administration of levosimendan as an adjunct to advanced life support in refractory OHCA. Secondary outcomes will include key clinical and functional measures. The results will inform the design of a larger, definitive trial.

## Methods

2

### Trial Design

2.1

This will be an investigator‐initiated, randomized, double‐blind, placebo‐controlled, single‐center pilot trial conducted in Stockholm County, Sweden. It is designed to explore the effect of levosimendan, administered prehospitally during ongoing advanced life support, on 30‐day mortality. A schematic study flow diagram is presented in Figure 1. The estimated study period is 18 months. The study is preregistered in the Clinical Trials Information System (CTIS) (EU Clinical Trial No.: 2024‐517279‐20‐02) and ISRCTN at https://www.isrctn.com/ (ISRCTN15862521; October 22, 2025). The results will be reported according to the CONSORT Statement [36].

**FIGURE 1 aas70159-fig-0001:**
[figure not shown]
Study flow diagram. ALS, advanced life support; ECPR, extracorporeal cardiopulmonary resuscitation; OHCA, out‐of‐hospital cardiac arrest; ROSC, return of spontaneous circulation.

### Inclusion Criteria

2.2

To be eligible for inclusion in the trial, patients must meet all of the following criteria:
Age 18–75 yearsWitnessed OHCAPrompt start of CPR (i.e., within 2 min)First recorded rhythm ventricular fibrillation or pulseless ventricular tachycardia, or pulseless electrical activity in cases of suspected pulmonary embolism (as determined by the attending emergency medical service [EMS] physician)Refractory cardiac arrest, that is, sustained beyond third rhythm checkIntravenous access

### Exclusion Criteria

2.3

Patients must not be included in this trial if *any* of the following criteria are met:
Traumatic cause of cardiac arrestFirst recorded rhythm asystoleTime to administration of study drug > 30 min after onset of cardiac arrestKnown or apparent pregnancyKnown preexisting advanced malignancy, severe neurological or systemic disease, advanced cardiac or pulmonary disease, end‐stage chronic kidney disease requiring dialysis, or ongoing bleedingKnown preexisting (i.e., current) *Do Not Attempt CPR* order

### Screening and Randomization

2.4

Screening and enrollment will be conducted by the attending EMS physician, who assesses whether resuscitation attempts are appropriate and whether the patient meets all eligibility criteria. Eligible patients will then be enrolled and randomized in a 3:1 ratio (levosimendan:placebo) using block randomization with a block size of four.

Given the emergency setting, prefilled, numbered syringes will be supplied to each EMS team. These visually identical syringes contain either levosimendan or placebo, thereby ensuring blinding of patients, clinicians, and trial personnel. Allocation is operationalized by administration of the study drug. Patients will be enrolled consecutively.

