### Blinding

2.6

The study drug will be prepared in‐hospital by personnel not involved in the trial, and dispensed into identical, blinded syringes bearing neutral study labels. This ensures blinding of patients, EMS physicians, paramedics, and the trial team. Only an external research nurse, independent of the study, will have access to the randomization list linking syringe numbers to treatment allocation.

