### Study Outcomes

2.8

The primary endpoint is 30‐day survival.

Secondary endpoints comprise a series of clinical outcomes intended to capture both early and downstream effects of the intervention. These include:
Conversion to a potentially perfusing rhythm (except ventricular tachycardia) among participants without such rhythm at study inclusion;Return of spontaneous circulation (any, or sustained [≥ 20 min]), defined as the return of spontaneous pulse or blood pressure as determined by the treating clinician;Survived event, defined as ROSC sustained until arrival at the emergency department and transfer of care to medical staff at the receiving hospital;Transport to hospital;Hospital arrival status (i.e., condition at hospital arrival: ROSC, CPR in progress, deceased);Number and duration of vasopressor infusions (duration > 1 h) in the intensive care unit (ICU) up to 72 h (e.g., norepinephrine, epinephrine, phenylephrine, vasopressin, dopamine, methylene blue);Number and duration of inotrope infusions (duration > 1 h) in the ICU up to 72 h (e.g., epinephrine, dobutamine, milrinone, levosimendan);Mechanical circulatory support in the ICU within 7 days (e.g., veno‐arterial extracorporeal membrane oxygenation, Impella device, intra‐aortic balloon pump);Type and degree of organ dysfunction (e.g., renal, hepatic, or cardiac; exploratory);Neurological outcome at hospital discharge (i.e., cerebral performance category [CPC] 1–2 vs. 3–5);Circumstances of death;Plasma concentration of levosimendan and its metabolite (repeated samplings during the first 72 h); andOrgan donation (i.e., ≥ 1 solid organ donated for transplantation).

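### A fixed block of four at 3:1, published before the first patient, makes later allocations deducible if a placebo is unmasked while its block is open

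*Protocol article*

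**What the plan says.** The Abstract (Methods) gives the design: "Forty patients will be randomized in a 3:1 ratio", 30 to levosimendan and 10 to placebo. Section 2.4 (Screening and Randomization) adds that allocation is made "using block randomization with a block size of four". No other block size and no stratification factor is stated, and section 2.1 describes a single-center trial.

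Section 2.4 also says that "prefilled, numbered syringes will be supplied to each EMS team" and that "Screening and enrollment will be conducted by the attending EMS physician", who also judges whether resuscitation is appropriate. Syringes look identical and patients are to be enrolled consecutively. Section 2.6 (Blinding) restricts the key: "Only an external research nurse, independent of the study, will have access to the randomization list linking syringe numbers to treatment allocation".

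Section 2.8 lists "Plasma concentration of levosimendan and its metabolite" as a secondary endpoint, sampled repeatedly over the first 72 h, and leaves the determination of ROSC to the treating clinician. Section 2.7 allows levosimendan in intensive care in either arm. The article is dated 24 November 2025, and section 2.16 plans the start for January 2026.

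**The concern.** Identical syringes and a locked list protect against reading an allocation directly. They do not protect against deducing one from a known block structure. At 3:1, four is the smallest block possible, so each block contains a single placebo. Once that placebo is identified, nothing in the rest of the block is random to whoever knows it.

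The people who could use such knowledge are close to the decisions that matter. The attending EMS physician decides on eligibility and on whether resuscitation is appropriate, and ROSC is a clinician's judgement. The primary endpoint, 30-day survival, is objective, but it can still be moved by who is enrolled and how long resuscitation continues. With 10 placebo patients, one patient is 10 percentage points of that arm's survival.

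**Working it through.** **Inputs.** N = 40, ratio 3:1 and group sizes 30 and 10 (Abstract); block size 4 (section 2.4); estimated study period 18 months (sections 2.1 and 2.16). The leak probability q below is an assumption; the article gives no such figure.

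**Reproducing the plan's figures.** 40/4 = 10 blocks, each with 3 levosimendan and 1 placebo, gives 30 and 10, as stated.

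**One revealed allocation.** It is the placebo with probability 1/4, and then the other three are certain. It is levosimendan with probability 3/4; one placebo is then left among three syringes, so each has placebo probability 1/3 instead of 1/4 and nothing is certain. Two revealed allocations settle the block with probability 1/2; three always do.

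**Worst case: every earlier allocation in the block is known.** An assignment is certain in advance when only one type is left, so the expected number of certain assignments is the expected length of the final run of one type. With a active and p placebo in random order this is a/(p+1) + p/(a+1).

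- Block of four: 3/2 + 1/4 = 1.75 of 4, or 43.75%. Over 10 blocks this is 17.5 of 40.
- Single 30:10 list: 30/11 + 10/31 = 2.73 + 0.32 = 3.05 of 40, about 8%.

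**Partial leak: each earlier allocation becomes known independently with probability q.** In a block of four the chance that an assignment is certain in advance is:

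- position 1: 0
- position 2: q/4
- position 3: 2q/4
- position 4: 3q/4 + q³/4

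The sum is 1.5q + q³/4 per block, multiplied by 10 for the trial.

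| q (assumed) | certain per block | certain of 40 |
|---|---|---|
| 0.10 | 0.150 | 1.5 (3.8%) |
| 0.25 | 0.379 | 3.8 (9.5%) |
| 0.50 | 0.781 | 7.8 (19.5%) |
| 1 | 1.750 | 17.5 (43.75%) |

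Every row also assumes that the observer can tell which syringes share a block.

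**How long a block stays open.** With even recruitment over 18 months and one list used in order, a block takes about 18 × 4/40 = 1.8 months. That is long compared with 72 h of sampling, so an assay reported promptly could arrive while its block is open. An assay run after recruitment could not.

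**Alternative: blocks of 4, 4, 8, 12 and 12.** They total 40 and hold 1 + 1 + 2 + 3 + 3 = 10 placebo, so 30:10 is kept. By the same formula a block of 8 gives 6/3 + 2/7 = 2.29 and a block of 12 gives 9/4 + 3/10 = 2.55. Even if the sizes and boundaries became known, the worst case would be 2 × 1.75 + 2.29 + 2 × 2.55 = 10.9 of 40, against 17.5. While they stay undisclosed, a known placebo no longer settles the following syringes, because the block may hold more than one.

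**The case against.** The strongest reply is that this is a double-blind trial. Predictable blocks are chiefly a danger where allocations are seen after assignment. Here the syringes are identical, the trial team is blinded and one independent nurse holds the list. Without an unmasked allocation, the block size gives nothing away. That stands, and it is why the point is conditional.

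Three stronger readings might be inferred, and the documents do not support them.

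- *Any single revealed allocation discloses the block.* This is true only when it is the placebo, 1 time in 4.
- *The plasma assays are a leak.* Section 2.8 lists them as an endpoint and does not say that results reach anyone during the trial. Their handling is the kind of detail an article may leave to the full protocol, so silence is no fault. Because section 2.7 permits levosimendan in intensive care in both arms, a positive level does not prove the active arm. Only a result without drug would point to placebo, and only in patients who lived long enough to be sampled.
- *Hypotension or emergency unblinding would reveal the arm.* Section 2.9 describes circulatory instability and arrhythmias as common after arrest and attribution to the drug as difficult. The article describes no unblinding procedure.

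It is also fair that section 2.4 does not say that syringe numbers run in block order or that a block stays with one EMS team. Enrolment is to be consecutive, and 30-day survival comes from records and not from judgement. Finally, small blocks have a benefit: used in order, they give exactly 5 placebo among the first 20 patients. A single 30:10 list would give 3 or fewer with probability 13.7% (hypergeometric).

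None of this removes the core. The block size is stated and public, and no stratification is stated that would require so small a block.

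**Conclusion.** The point holds as a cheap improvement to allocation concealment, not as evidence that blinding will fail. The fixed, published block of four means that a placebo unmasked while its block is open identifies every syringe left in that block.

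The 44% (17.5 of 40) is a ceiling and should not be read as an expected rate: it needs all earlier allocations and block membership to be known. Under assumed leak probabilities of 10% to 50%, about 1.5 to 8 of 40 assignments would be certain in advance, still provided that block membership is known. The article does not allow q to be estimated, and q may be zero if the assays are masked.

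**What to change.** Before the first patient:

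1. Regenerate the list with varying block sizes in random order, constrained to total 40, and do not disclose the sizes. An example of the form is 4, 4, 8, 12 and 12, which keeps 30:10; the actual set should stay confidential. The constraint matters: blocks of 4, 8 and 12 drawn freely with equal probability end exactly at 40 only about half the time.
2. Number the syringes so that the numbers do not reveal which ones share a block.
3. Confirm in the laboratory instruction that levosimendan and metabolite results stay out of the medical record and away from the trial team until database lock. If the full protocol already says so, nothing needs to change here.

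If syringes have already been prepared, apply the new list to those not yet prepared.

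The cost is one new list and at most one line of instruction. The statistical price is slightly looser balance over calendar time or if recruitment stops early. Inside an unfinished block of 12, the placebo count can be at most 3 × 3/4 = 2.25 patients away from its 3:1 share, against 0.75 in a block of four. A single 30:10 list lowers predictability further, but it could be up to 10 × 3/4 = 7.5 patients away, so the constrained blocks are the better compromise for a pilot that may stop short.

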### Intervention

2.5

Patients randomized to the treatment group will receive a single intravenous bolus of levosimendan (2.5 mg in 49 mL of 5% glucose; concentration 0.05 mg/mL) administered during CPR via a prefilled, blinded syringe. Patients in the placebo group will receive an equivalent intravenous injection of 50 mL of 5% glucose, also administered during CPR from a prefilled, blinded syringe. The study drug will be administered manually as rapidly as possible and only once. Included patients will be transferred to Karolinska University Hospital in Solna, Stockholm, Sweden, unless resuscitation efforts are terminated out‐of‐hospital.

### Blinding

2.6

The study drug will be prepared in‐hospital by personnel not involved in the trial, and dispensed into identical, blinded syringes bearing neutral study labels. This ensures blinding of patients, EMS physicians, paramedics, and the trial team. Only an external research nurse, independent of the study, will have access to the randomization list linking syringe numbers to treatment allocation.

### General Management of Advanced Life Support and Postresuscitation Care

2.7

General management of cardiac arrest will follow local protocols both in the out‐of‐hospital and in‐hospital settings. Adherence to current European and national guidelines for advanced life support and postresuscitation care is strongly recommended. The use of levosimendan at established doses as an adjunct to intensive care after hospital admission will remain at the discretion of the treating physician.

### Study Outcomes

2.8

The primary endpoint is 30‐day survival.

Secondary endpoints comprise a series of clinical outcomes intended to capture both early and downstream effects of the intervention. These include:
Conversion to a potentially perfusing rhythm (except ventricular tachycardia) among participants without such rhythm at study inclusion;Return of spontaneous circulation (any, or sustained [≥ 20 min]), defined as the return of spontaneous pulse or blood pressure as determined by the treating clinician;Survived event, defined as ROSC sustained until arrival at the emergency department and transfer of care to medical staff at the receiving hospital;Transport to hospital;Hospital arrival status (i.e., condition at hospital arrival: ROSC, CPR in progress, deceased);Number and duration of vasopressor infusions (duration > 1 h) in the intensive care unit (ICU) up to 72 h (e.g., norepinephrine, epinephrine, phenylephrine, vasopressin, dopamine, methylene blue);Number and duration of inotrope infusions (duration > 1 h) in the ICU up to 72 h (e.g., epinephrine, dobutamine, milrinone, levosimendan);Mechanical circulatory support in the ICU within 7 days (e.g., veno‐arterial extracorporeal membrane oxygenation, Impella device, intra‐aortic balloon pump);Type and degree of organ dysfunction (e.g., renal, hepatic, or cardiac; exploratory);Neurological outcome at hospital discharge (i.e., cerebral performance category [CPC] 1–2 vs. 3–5);Circumstances of death;Plasma concentration of levosimendan and its metabolite (repeated samplings during the first 72 h); andOrgan donation (i.e., ≥ 1 solid organ donated for transplantation).

### Adverse Events

2.9

Patients experiencing cardiac arrest commonly develop complications related to the precipitating cause, the acute condition itself and associated global ischemia–reperfusion injury, resuscitation efforts (e.g., chest compressions, defibrillation), and postresuscitation care. Such complications may include circulatory instability, arrhythmias, organ dysfunction or failure, and metabolic and electrolyte disturbances. Thus, distinguishing adverse events directly attributable to the intervention from those inherent to the underlying condition is challenging.

In this trial, potential adverse events will be systematically recorded and compared between treatment groups to identify any imbalance suggestive of a drug‐related effect. Clinical data will be collected up to 3 days following inclusion, and medical records will be reviewed at Day 30 to capture any delayed or secondary effects. At Day 30, medical records will be scanned for other potential side effects. Particular attention will be paid to hemodynamic instability, including recurrent or prolonged hypotension, increased requirements for vasoactive agents or mechanical circulatory support, and new or worsening arrhythmias. Only events that are unexpected or considered possibly related to the study drug will be reported to and reviewed by the trial management committee.

### Follow‐Up

2.10

Follow‐up will be conducted using prospectively collected clinical data. Information on 30‐day survival, neurological outcome (assessed using the CPC scale), and organ function will be obtained from electronic medical records. No additional in‐person visits or direct contact with participants or their next of kin will be required.

### Data Collection and Management

2.11

Individual participant data, including background characteristics, clinical findings, laboratory results, and resuscitation metrics such as CPR quality and timing, will be collected from the EMS physician, ambulance reports, and medical records. Key variables will include neurological status, hemodynamic parameters, organ function and medication use (e.g., vasoactive and inotropic agents), and the need for mechanical circulatory support.

All data will be entered by site personnel into a secure, web‐based electronic case report form. The trial database will be hosted and maintained on a secure server managed by the study center.

### Sample Size and Power Estimations

2.12

As this is, to the best of our knowledge, the first trial designed to investigate the effect of intra‐arrest levosimendan in OHCA, no prior effect estimates are available. The purpose of this pilot study is to explore the effects of levosimendan compared with placebo and to estimate the potential effect size on 30‐day survival and secondary outcomes. Accordingly, no formal power calculation was performed; we estimated that enrolling 40 patients would be sufficient to detect a potential signal of effect.

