### Statistical Analyses

2.13

All analyses will follow the intention‐to‐treat principle, with complementary per‐protocol analyses performed to assess drug‐specific effects. Continuous variables will be summarized as mean ± standard deviation or with 95% confidence intervals, or as median with interquartile range, as appropriate. Categorical variables will be reported as counts and percentages.

The primary outcome will be analyzed using Cox proportional hazards regression and illustrated with Kaplan–Meier survival curves. Sensitivity analyses of the primary outcome will include adjustment for baseline characteristics. Secondary outcomes will be compared between groups when applicable using appropriate statistical tests depending on the variable. All statistical tests will be two‐sided, with a significance level set at *p* < 0.05.

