### Strengths and Limitations

3.1

A key strength of this pilot study is the robust preclinical evidence supporting levosimendan in cardiac arrest, demonstrating improved outcomes across several animal models. Since its market introduction in Sweden in 2000, levosimendan has become one of the most extensively studied cardiovascular drugs, with a substantial evidence base and broad clinical experience in severely ill patients with cardiac failure. Safety data are reassuring, with few major adverse events apart from hypotension reported when used as indicated [14]. Conducting the pilot trial at a single center with comprehensive resuscitation resources, around‐the‐clock interventional cardiology, extracorporeal CPR, cardiothoracic surgery and intensive care, and pharmacologic laboratory support, further strengthens feasibility and relevance. The pilot study design is essential for generating preliminary data on clinical outcomes, safety, and feasibility in this challenging setting.

Limitations include the small sample size and single‐center design, which constrain statistical power and limit generalizability.

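### The statement that 40 patients suffice to detect a potential signal of effect is unsupported, and for 30-day survival it does not hold for any realistic effect

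*Protocol article*

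**What the plan says.** The abstract sets the size and split: "Forty patients will be randomized in a 3:1 ratio", which gives 30 patients on levosimendan and 10 on placebo. Under Study Outcomes, "The primary endpoint is 30‐day survival". Section 2.12 explains that no earlier effect estimates exist, that the pilot is to explore effects and estimate a potential effect size on 30-day survival and secondary outcomes, and that "no formal power calculation was performed". The same sentence then ends: "we estimated that enrolling 40 patients would be sufficient to detect a potential signal of effect".

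Section 2.13 adds the analysis: "The primary outcome will be analyzed using Cox proportional hazards regression". It continues "All statistical tests will be two‐sided, with a significance level set at" p < 0.05. Section 3.1 concedes: "Limitations include the small sample size and single‐center design, which constrain statistical power".

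**The concern.** A pilot may reasonably go without a power calculation, and that is not the fault here. The fault is the positive claim about what the design can do. Section 2.12 offers sufficiency to detect a signal as the reason for 40 patients, but gives no size of signal, no control survival, no threshold and no calculation. Section 3.1 points the other way.

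What is at stake is how the result will be read. The article says the findings will inform a definitive multicentre trial. If readers have been told that 40 patients are enough to show a signal, a chance difference in survival may be taken as one, and a flat or negative difference as its absence.

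**Working it through.** **Inputs from the article.** 30 versus 10 patients (abstract); 30-day survival as primary endpoint (2.8); two-sided 0.05 and Cox regression (2.13). The article gives no power, effect size or control survival for this population. The Introduction says only that 30-day survival is below 14% for all out-of-hospital arrest in Sweden. The trial selects a more favourable group, so control survival is taken here as 5% to 30%, an assumption.

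**The article's own figure.** The total of 40 cannot be reproduced, because no inputs to it are stated.

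**1. Apparent gain when there is none.** Let X ~ Bin(30, p) and Y ~ Bin(10, p) be independent, and sum the exact probabilities of all outcomes with X/30 − Y/10 ≥ 0.10. The 10-point yardstick is chosen here, since the protocol names none.

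| Survival in both arms | Gain ≥ 10 points | Gain > 10 points |
|---|---|---|
| 5% | 11% | 4% |
| 10% | 23% | 13% |
| 14% | 27% | 18% |
| 20% | 30% | 22% |
| 30% | 32% | 25% |

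The lower rates at 5% and 10% survival do not rescue the claim: one placebo survivor or fewer is then expected (10 × 0.10 = 1). At 10% survival the chance of no placebo survivor is 0.9^10 = 35%.

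**2. No apparent gain when there is one.** With a true 10-point gain, the observed difference is zero or negative in 23% (10% vs 20%), 26% (14% vs 24%), 28% (20% vs 30%) and 31% (30% vs 40%) of trials.

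**3. Power at two-sided 0.05.** Fisher's test by exact enumeration. For Cox, the Schoenfeld approximation: power = Φ(√(d × 0.75 × 0.25) × |ln HR| − 1.96), with HR = ln(treated survival)/ln(control survival) and d the expected deaths.

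Example, 20% vs 40%: HR = ln 0.4/ln 0.2 = 0.569; d = 30 × 0.6 + 10 × 0.8 = 26; √(26 × 0.1875) × 0.563 − 1.96 = 1.244 − 1.96 = −0.716; power = 24%.

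| Control survival | +10 points: Fisher | +10 points: Cox | +20 points: Fisher | +20 points: Cox |
|---|---|---|---|---|
| 10% | 2% | 14% | 15% | 34% |
| 14% | 4% | 12% | 15% | 28% |
| 20% | 5% | 10% | 14% | 24% |
| 30% | 5% | 9% | 12% | 20% |

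**4. Effect needed for 80% power.** With 20% control survival, Fisher's test first reaches 80% at about 74% treated survival. The Cox approximation agrees. At 73%, HR = ln 0.73/ln 0.2 = 0.196 and d = 30 × 0.27 + 10 × 0.8 = 16.1, so √(16.1 × 0.1875) × 1.632 − 1.96 = 0.88, a power of 81%. Even if deaths are counted as though treatment prevented none (d = 40 × 0.8 = 32), the detectable HR is exp(−(1.96 + 0.84)/√(32 × 0.1875)) = 0.32, which is 20% vs about 60%.

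**5. Precision.** At 20% survival in both arms, the 95% half-width for the difference is 1.96 × √(0.2 × 0.8 × (1/30 + 1/10)) = 0.286, about 29 points. It is 21 points at 10% survival and 33 points at 30%. An observed 2/10 on placebo has an exact 95% interval of 3% to 56%.

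**6. Role of the split.** With 20 versus 20, the chance of an apparent gain of at least 10 points under no effect is 24% at 14% survival, 28% at 20% and 30% at 30%. With 30 versus 10 it is 27%, 30% and 32%.

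**The case against.** The strongest reply is that the sentence claims no power. It speaks only of a potential signal, in a trial called a pilot throughout, whose purpose is to explore and estimate, and whose limits are disclosed in section 3.1. Much of this stands. An undefined claim cannot be refuted outright, and the 10-point yardstick and the control rates are not the protocol's. Part of the rate in the first table comes from outcomes at exactly 10 points, which is why both columns are shown. Limited power and the hope of seeing something are in tension more than in flat contradiction. But whether a signal means a p-value, a point estimate or an interval, 30 versus 10 does not separate a plausible survival effect from none. If the phrase means nothing testable, it cannot justify the sample size.

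Three stronger readings are tempting, and the documents do not support them:

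- **That the 3:1 allocation is the cause.** Equal arms of 20 do only slightly better.
- **That the trial can show nothing on any outcome.** Only 30-day survival was examined. Section 2.12 also covers secondary outcomes such as return of circulation, rhythm conversion and drug concentrations, on which these calculations are silent.
- **That a chance result would start or stop the definitive trial, or fix its assumed effect.** No go/no-go rule is stated; the article says only that results will inform the design.

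**Conclusion.** The concern holds for the primary endpoint. Section 2.12 states a capability without support, and for 30-day survival the design does not have it for any realistic effect. This does not depend on the choice of test: power for a 20-point gain is at most about one in three under the planned Cox analysis and about one in seven by Fisher's test, over control survival of 10% to 30%. How often chance alone mimics a 10-point gain does depend on the assumptions: about three in ten at 14% to 30% survival, less if survival is lower or if the gain must exceed 10 points. The Cox figures assume proportional hazards and use a large-sample approximation that is rough with so few patients.

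This is a wording correction that should be made. It is not a defect in enrolment, randomisation or endpoints, and it does not have to be resolved before the trial can proceed.

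**What to change.** In section 2.12, delete the sufficiency claim and keep the statement that no power calculation was done. Put the expected precision in its place, with the assumed survival named: for example, at 20% survival in both arms the 95% confidence interval for the difference extends about 29 points either side, and 2 survivors among 10 placebo patients would have an exact interval of 3% to 56%.

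Add that 30-day survival will be reported as an estimate with its confidence interval, that no efficacy conclusion will rest on it, and that the observed difference will not by itself set the effect assumed for the definitive trial. Sections 2.12 and 3.1 would then agree.

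The cost is a few sentences and a less favourable description of what the pilot can deliver. No extra patients are needed, and the allocation and endpoints stay as they are.
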